### Participants

The participants of this study will be employees of a tertiary hospital, from any section, with any complaints of pain or discomfort in the upper extremity during the past 12 months. Potential subjects will be recruited by verbal invitation, posters and institutional cell phone messages. Inclusion and exclusion criteria are described in Table 1. All participants will sign a written informed consent form before participating.

**Table 1 Tab1:** The Inclusion and Exclusion criteria description

Inclusion Criteria	Exclusion Criteria
• > 18 years old; • both sexes; • provide written consent; • workers who have musculoskeletal complaints in the past 12 months in the cervical region, shoulder, elbow, wrist or hand and/or fingers, without a clinical diagnosis; • workers who are not away from their professional activities.	• pregnancy; • congenital spinal abnormality and significant musculoskeletal deformities (such as amputation, dysmetria); • severe cervical spine disorders, postoperative conditions in the neck or upper limb region; • uncontrolled cardiovascular disease, cardiac arrhythmia, angina or related symptoms, and postural hypotension or other contraindication for physical exercise; • workers who engage in some form of regular exercise, which involves strengthening exercises and muscle resistance; • workers who have diagnosis of musculoskeletal dysfunction of the upper extremity and are undergoing physiotherapy treatment.

### Randomization

Employees who agree to participate will be randomized in a 1:1 ratio by a random allocation sequence by concealment envelopes in two parallel groups: control group (CG) and workplace exercise group (WEG).

### Blinding

Due to the nature of this study, it is not possible to fully blind the research participant or the clinician investigator providing the intervention. Randomization will be blinded for the outcome data collection and statistician assessors.

### Procedures for the experimental proposal of intervention

#### Control group

Participants in the CG will receive ergonomic guidance. The protocol will be composed by group lectures, digital handouts and specific ergonomic orientations and suggestions of low-cost changes in each participant’s workplace. The content of lectures and digital handouts will comprise information about what are WRMDs and how to prevent them and general posture and ergonomic guidelines, both for daily living and occupational activities.

#### Workplace exercise group

In addition to the ergonomic guidance, the WEG group will attend exercise sections 3 times/week, for 12 weeks. Exercise sections will take place inside the hospital, according to the workers’ availability during the breaks within working hours and will last 20 min. They will be divided as follows:Five-minute warm-up movements (3 × 15 repetitions each);Ten minutes of specific resistance strengthening exercises (3 × 10 repetitions each);Five minutes of stretching and relaxing movements (3 × 30 seconds each).

Resistance strengthening exercises for cervical region and upper extremity will be performed with individually defined load and progression. The movements will be: flexion, abduction and shoulder elevation in the scapular plane; external shoulder rotation; “push up” on the wall; elbow flexion associated with pronation (concentric) and supination (eccentric) and manual grasping (Additional file 1: Appendix 1). Regarding the intervals between the movements, active recovery will be adopted to neutralize the effects of muscle fatigue. The criteria for interruption will be pain that incapacitates the execution of the movement, pain and /or discomfort or sensory alterations such as tingling and numbness.

Two physiotherapists with the collaboration of an undergraduate student will conduct the intervention. Sections will happen in small groups (Fig. 2), favoring social contact and integration among the employees, with the intention to improve the employee’s mood, as well as their adherence to the protocol.

**Fig. 2 Fig2:**
[figure not shown]
Small group exercises

#### Outcome measures

##### Demographic information

Participants will be interviewed and assessed for demographic and descriptive information including age, sex, weight, and height for the body mass index (BMI) calculation, history of smoking or alcoholism, dominance, occupation, work task (repetitive movements, and vibration), time of service, if any previous history of injury and symptoms perceived in the cervical region and upper limbs (intensity of pain, location and duration of the symptoms). Demographic information will be collected at the baseline examination only.

Additionally, the following self-reported questionnaires will be applied:The International Physical Activity Questionnaire (IPAQ) short version, to characterize the sample as very active, active and irregularly active [33].The Global Lateral Preference Inventory (GLPI) [34] to assess laterality and manual preference. The subject can fill out the activities according to his/her preference in the options: always left, majority left, indifferent, majority right, always right and I don’t know. Each of these answers has a different score. At the end, punctuation will be summed to generate the qualitative classification

##### Primary outcome measures

Pain: assessed by the Numerical Pain Scale (NPS) [35].Mean isokinetic peak torque: workers will be submitted to the upper limb strength assessment in the isokinetic dynamometer Biodex System 4 Pro™, following all the calibration and use recommendations referred by the manufacturer in the manual “Biodex multi-joint system - pro setup/operation manual”. Based on Prentice and Voight (2003) [36], all movements will be performed at a speed of 60°/sec. The dynamometer positions will be based on the positioning guidance material, except for the scapular plane elevation that was adapted for this study, based on Kapandji (2000) [37]. The movement to be tested in isokinetic mode will be shoulder elevation in the plane of the scapula. The test will consist of 5 direct repetitions, with the volunteer being instructed to perform his maximum force during all repetitions, with an interval of 3 min between one segment and another [38]. Isokinetic tests will be done bilaterally to collect the parameters of the mean peak torque in Newton (N).Isometric palmar grip strength: will be measured by the JAMAR™ dynamometer, an instrument recommended by the American Society of Hand Therapists (ASHT) because of its reported reliability and validity [39].

##### Secondary outcome measures

Fatigue: muscle performance will be assessed through the *The Functional Impairment Test-Hand and Neck/Shoulder/Arm (FIT-HaNSA)* [40]. This device assesses fatigue resistance during tasks that simulate gross motor functions of the upper limb, such as reaching and picking up objects at different heights and working sustained above the head [40]. The test consists of three tasks: 1) a shelf is placed at waist level and one 25 cm above it, 3 containers of 1 kg are placed on the lowest shelf; using the committed arm, the volunteer must place the 3 containers, from one shelf to the other, at a speed of 60 beats/minute controlled by a manometer; 2) a shelf is placed at eye level and one 25 cm below it. Volunteers are again instructed to use their affected arm to take the 3 containers from one shelf to another at a speed of 60 beats/minute. 3) A plate containing screws is fixed perpendicularly to the shelf. Volunteers are instructed to use both arms to tighten and loosen screws repeatedly. Each task will be performed only once, for a maximum of 300 s, or when the volunteer uses the criteria for stopping the test, which are: perform compensation with uncorrected trunk movements in up to 5 successive repetitions, interrupt the test due to extreme pain or fatigue or inability to complete 1 repetition of the movement within 2 beats of the metronome for 5 successive repetitions.Map of pain description: Nordic Questionnaire will be applied [41].Patient Specific Functional Scale (PSFS) [42], QuickDASH questionnaire [43], Work Ability Index (WAI) [44, 45], Need for recovery (NFR) [46] and Neck Disability Index [47] self-reported questionnaires will be applied.

Both primary and secondary outcome measures will be collected at baseline and after 12 weeks of intervention for all volunteers. Work ergonomic evaluation will be a complementary analysis, which integrates the scope of secondary outcome measures and also collected at baseline and after 12 weeks for both groups.

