**Methods:**

This trial was designed according to the Consolidated Standards of Reporting Trials - CONSORT guidelines. Participants will be employees of a tertiary hospital, with any complaints of pain or discomfort in the upper extremities during the past 12 months, without clinical musculoskeletal diagnosis. 166 participants will be randomized into parallels groups as control and workplace exercises. The primary outcomes will be Numerical Pain Scale, isokinetic muscle strength of abduction and isometric handgrip strength. Secondary outcomes on discomfort, fatigue, work capacity and dysfunction will be assessed by QuickDASH, Patient Specific Functional Scale, Neck Disability Index, Need for recovery, Work Ability Index self-report questionnaires and FIT-HANSA performance test. The Ergonomic Work Analysis will be done by Quick Expose Check, RULA, REBA, RARME, ROSA and HARM risk assessment ergonomic tools. We will analyze the difference between baseline and 12 weeks of intervention by T test of independent samples (95% confidence interval, *p* < 0.05). Clinical significance will be analyzed by the minimum clinically important difference and effect size by Cohen index. The association between the variables will be analyzed by construct validity with the hypothesis of correlations between pain and muscle strength, strength and functionality and strength and fatigue.

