### Statistical approach

An investigator will receive the encoded data and perform the statistical analysis entered into a database Excel spreadsheet. The Kolmogorov-Smirnov test will be used to verify the normality distribution of the data. Descriptive statistics (frequencies, means, standard deviation, confidence interval) will be used to analyze the sociodemographic characteristics of the participants. The significant statistical difference between the outcome groups will be analyzed by the T test of independent samples to compare the means at the baseline and after 12 weeks of intervention, using as outcome variables the numeric pain scale, the mean isokinetic scores of peak torque and work, the patient self-reported questionnaires, with 95% confidence interval, *p* < 0.05. Responsiveness values for interventions to changes in clinical significance will be defined to score the minimum clinically important difference [56]. The Cohen Index will be defined to calculate the effect size, considering 0.3 low, 0.5 moderate and 0.8 high effect [57]. The association between the variables will be analyzed through the construct validity by the hypothesis tests, which determine the convergent and discriminant validity [58, 59]. It is expected that there will be moderate inverse correlation between pain and muscle strength production, moderate correlation between strength production and functionality and strong to moderate correlation between strength production and fatigue endurance. The statistical program SPSS Statistics 20.0 will be used for all analyses [57, 60].

The confounding factors that could be accounted for in the statistical plan and potential to bias even with the randomization process are: occupations will be analyzed together for comparations between control and intervention groups, before and after the intervention but not in subgroups by level of activity load; and intention-to-treat analysis will be performed including data for the noncompliance volunteers, in exception for dropout cases due to loss of follow-up [61].

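### FIT-HaNSA task times stop at 300 s, and the only between-group test named, a t test on change, understates endurance gains to the extent that workers reach that cap

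*Protocol article*

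**What the plan says.** FIT-HaNSA is the measure placed under fatigue among the secondary outcomes (protocol article, Secondary outcome measures), and the article says of it: "This device assesses fatigue resistance during tasks that simulate gross motor functions of the upper limb". It has three tasks, and the scoring limit is explicit: "Each task will be performed only once, for a maximum of 300 s, or when the volunteer uses the criteria for stopping the test".

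The Methods paragraph of the abstract lists FIT-HaNSA among the secondary outcomes and then gives one method, with no outcome exempted: "We will analyze the difference between baseline and 12 weeks of intervention by T test of independent samples". The Statistical approach section describes the t test as "using as outcome variables the numeric pain scale, the mean isokinetic scores of peak torque and work, the patient self-reported questionnaires". FIT-HaNSA is not on that list. That section also plans a normality check, without naming an alternative if it fails. It adds Cohen's index for effect size and an expected correlation between strength and fatigue endurance.

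Table 1 (Participants) admits "workers who are not away from their professional activities" and "workers who have musculoskeletal complaints in the past 12 months in the cervical region" or upper limb, without a clinical diagnosis. Symptoms at entry are not required. The article gives no FIT-HaNSA mean, SD or expected share at 300 s.

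**The concern.** A time recorded as 300 s because the task ended is right-censored. A t test on change treats it as the true endurance time. A worker capped at both visits contributes a change of zero, whatever was gained in between. The hypothesis is that exercise improves endurance, so the exercise arm would have more workers at the cap by week 12 and would lose more of its gain.

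Eligibility makes a ceiling plausible: participants are at work, have no diagnosis, and may have had their complaint months earlier. Reducing fatigue is part of the stated aim. If many workers reach 300 s, a null FIT-HaNSA result could reflect the limit of the test and not a lack of effect. The planned strength–fatigue correlation would also tend to be weakened.

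**Working it through.** **The plan's own figure.** The article has none for FIT-HaNSA. Its one computed figure, 75 per group (Sample size calculation), rests on pain and peak torque. With effect size 0.5, two-sided 0.05 and 80% power, a t test needs 64 per group, so 75 is not reproduced. That is a separate matter. Here 75 is used only as the number analysed per arm.

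**Assumptions (not in the article).** Latent endurance is normal with SD 1. Controls do not change. The true gain is 0.5 SD. The baseline-to-week-12 correlation is 0.6. A share p of controls is at the cap, and the same share of both arms at baseline.

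**Step 1: mean difference.** For latent mean μ and cap c,

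E[min(X, c)] = μΦ(c−μ) − φ(c−μ) + c[1 − Φ(c−μ)].

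- p = 10%, c = 1.282. Control: −0.1755 + 1.282 × 0.10 = −0.047. Exercise: 0.5 × 0.7828 − 0.2939 + 1.282 × 0.2172 = 0.376. Difference 0.423, and 0.423/0.5 = 85% kept.
- p = 40%, c = 0.253. Control: −0.3863 + 0.253 × 0.40 = −0.285. Exercise: 0.5 × 0.4026 − 0.3870 + 0.253 × 0.5974 = −0.034. Difference 0.251, and 0.251/0.5 = 50% kept.

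Randomisation gives both arms the same expected capped baseline. It cancels, so the same shares apply to the difference in change.

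**Step 2: power.** Simulation with 75 per arm used 20,000 trials for the t test and 1,000 for the two models. ANCOVA here is ordinary regression of capped week-12 time on arm and baseline time. The Tobit model adds an indicator for a capped baseline and uses a likelihood-ratio test.

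| Controls at cap | Exercise arm at cap | Mean gain kept | Week-12 Cohen's d kept | Power: t test on change | Power: ANCOVA on capped times | Power: baseline-adjusted Tobit |
|---|---|---|---|---|---|---|
| 0% | 0% | 100% | 100% | 93% | 96% | – |
| 10% | 22% | 85% | 97% | 89% | 95% | 96% |
| 20% | 37% | 72% | 94% | 84% | 94% | 95% |
| 40% | 60% | 50% | 85% | 71% | 88% | 92% |
| 60% | 77% | 31% | 73% | 52% | 73% | 83% |

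Smaller runs under the same assumptions gave figures a few points lower in places, for example 67% to 69% for the t test on change at 40%. "About 70%" at 40% and "about 92%" uncapped are fair summaries.

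**Step 3: bias and error rate.** The Tobit estimate averaged 0.50 SD at every cap level, against a true 0.5. With no true effect, the t test on change rejected in about 5% of trials at every level.

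**Reading.** Much of the power recovered comes from adjusting for baseline and not from modelling the cap. At 20%, ANCOVA on capped times already reaches 94% against 95% for Tobit. The censored model's distinct contribution is to remove the understated difference. It adds material power only when many workers are capped (88% to 92% at 40%, 73% to 83% at 60%).

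**The case against.** **The ceiling is assumed.** The article gives no distribution of times, and some features point away from a large ceiling. The tasks are paced and loaded, include eye-level and overhead work, and end on trunk compensation, pain, fatigue or lost pace. Workers who already do strengthening exercise are excluded. This stands. A reader might infer that the t test understates any gain; the documents do not support that, because with nobody at 300 s nothing is lost.

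**The t test may not be meant for this outcome.** The Statistical approach section leaves FIT-HaNSA off its list, so the link rests on the abstract's general sentence. This stands as a limit on certainty. It does not remove the point: the abstract names FIT-HaNSA, exempts no outcome, and no other between-group method appears in the article.

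**Capped time is the score.** If the target is mean capped time, the t test is a valid comparison and type I error is not inflated. This also stands. A reader might infer that the test is invalid, and it is not. But the article says the test measures fatigue resistance, and a difference in capped times is an incomplete measure of that.

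**The size can be made to look worse than it is.** Cohen's d, the planned effect size, falls less than the raw mean because the cap also shrinks the SD (94% kept at 20% capped). Comparing a change-score t test with an adjusted Tobit model credits the censoring method with gains due to baseline adjustment. Both are correct, which is why the table shows ANCOVA separately.

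**It is one secondary outcome.** This is true, and the abstract's list of secondary outcomes also includes Need for Recovery, so the fatigue aim may not rest on FIT-HaNSA alone.

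**Conclusion.** The point holds conditionally. The 300 s cap is certain, and the only between-group method named ignores it. The consequence depends on the share of workers at the cap, which the article does not give. Under a normal latent time, a true gain of 0.5 SD, correlation 0.6 and 75 analysed per arm, the effect is small at 10% of controls capped (about 15% of the mean gain). It is substantial at 40% (about half of the mean gain, with power about 70% against about 92% uncapped).

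The direction is always toward understating a benefit, never toward a false positive. A reader might infer that the trial's main conclusions are at risk. They are not: the primary outcomes and the sample size do not use FIT-HaNSA. This is a cheap improvement to a secondary outcome.

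**What to change.** State the FIT-HaNSA analysis explicitly:

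- For each task, compare arms on week-12 time with baseline time as covariate, plus an indicator for a baseline at 300 s because that covariate is capped too.
- Treat 300 s as right-censored, by Tobit regression or a time-to-stop model.
- Report the share at 300 s by task, arm and visit.
- Keep the mean capped time, if wanted, as a descriptive or sensitivity result, and do not base the endurance effect size on the t test of capped changes.

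The cost is analysis wording only: no new data and no change to the test itself. The downside is that the effect becomes a modelled time difference or a hazard ratio, resting on a distributional assumption (Tobit) or on proportional hazards (Cox).

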##### Work ergonomic evaluation

For the worker’s biomechanical overload and occupational exposure risk levels classification the following instruments will be used: the Quick Exposure Check (QEC) [48], Rapid Upper Limb Assessment (RULA) [49], Rapid Entire Body Assessment (REBA) [50], Musculoskeletal Risk Assessment Measurement (RARME) [51], the translated version of Hand Arm Risk Assessment Method (HARM) [52] and the Rapid office strain assessment ROSA [53]. They will be applied based on direct and indirect observation by photographic and videos records of the body and the upper limbs in the more critical situations reported by workers. Work ergonomic evaluation will be performed by 2 physiotherapists familiar with the instruments, blinded for the division of interventional groups.

## Data analysis

### Sample size calculation

The a priori sample size calculation was performed by GraphPad Statemate™, with power of 80%, effect size of 0.5 and alpha level of 0.05, based on the Numeric Pain Rating Scale and the isokinetic scores of the mean peak torque of the abduction movement in the scapular plane [54]. Seventh five participants will be needed per group. A total of 166 participants with pain or discomfort complaints of upper extremity who meet the inclusion / exclusion criteria and consent to participate will be included in the study, considering 10% sample size loss and analysis per intent to treat [30, 55].

### Statistical approach

An investigator will receive the encoded data and perform the statistical analysis entered into a database Excel spreadsheet. The Kolmogorov-Smirnov test will be used to verify the normality distribution of the data. Descriptive statistics (frequencies, means, standard deviation, confidence interval) will be used to analyze the sociodemographic characteristics of the participants. The significant statistical difference between the outcome groups will be analyzed by the T test of independent samples to compare the means at the baseline and after 12 weeks of intervention, using as outcome variables the numeric pain scale, the mean isokinetic scores of peak torque and work, the patient self-reported questionnaires, with 95% confidence interval, *p* < 0.05. Responsiveness values for interventions to changes in clinical significance will be defined to score the minimum clinically important difference [56]. The Cohen Index will be defined to calculate the effect size, considering 0.3 low, 0.5 moderate and 0.8 high effect [57]. The association between the variables will be analyzed through the construct validity by the hypothesis tests, which determine the convergent and discriminant validity [58, 59]. It is expected that there will be moderate inverse correlation between pain and muscle strength production, moderate correlation between strength production and functionality and strong to moderate correlation between strength production and fatigue endurance. The statistical program SPSS Statistics 20.0 will be used for all analyses [57, 60].

The confounding factors that could be accounted for in the statistical plan and potential to bias even with the randomization process are: occupations will be analyzed together for comparations between control and intervention groups, before and after the intervention but not in subgroups by level of activity load; and intention-to-treat analysis will be performed including data for the noncompliance volunteers, in exception for dropout cases due to loss of follow-up [61].

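### The abstract and the Methods describe the between-arm t-test in two ways that do not match, and neither adjusts for the baseline value of the outcome

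*Protocol article*

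**What the plan says.** Two places in the protocol article state the main between-arm analysis.

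- Statistical approach: the difference between the groups is to be "analyzed by the T test of independent samples to compare the means at the baseline and after 12 weeks of intervention".
- Abstract, Methods: "We will analyze the difference between baseline and 12 weeks of intervention by T test of independent samples".

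Neither place names a covariate. The section on secondary outcome measures states that primary and secondary outcomes are all collected from every volunteer at baseline and again at 12 weeks. The Statistical approach section also lists occupation among possible sources of bias that remain despite randomisation, and then says "occupations will be analyzed together for comparations between control and intervention groups".

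The sample size section works "with power of 80%, effect size of 0.5 and alpha level of 0.05". It does not say whether that effect is in units of the 12-week SD or the SD of change.

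**The concern.** Taken at face value, the Methods sentence gives two tests per outcome. One is at baseline, where randomisation already makes any difference a matter of chance. The other is at 12 weeks and takes no account of where each person started. The abstract sentence gives one test, on change. These are different estimators with different variances, and the same data can be significant under one and not under the other. If the choice is left open until the data are seen, the 5% error rate of each single test no longer describes the procedure.

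Separately, both forms leave precision unused. The 12-week comparison gives the baseline value a coefficient of 0 and the change score gives it a coefficient of 1. ANCOVA estimates the coefficient from the data.

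**Working it through.** **Inputs from the protocol.** Effect 0.5 SD, alpha 0.05 (taken as two-sided), power 80%, 1:1 allocation, and "Seventh five participants will be needed per group".

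**Inputs assumed.** Baseline-to-12-week correlation rho of 0.3, 0.5 and 0.7; equal SDs at both visits; 0.5 in units of the 12-week SD. The documents give none of these.

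**The plan's own figure.** A two-sided t-test with effect 0.5, alpha 0.05 and 80% power needs 64 per arm (noncentral t), not 75. At 75 per arm the power is 86%, and 75 corresponds to an effect of about 0.46 at 80% power. The total of 166 does follow from 75: 75 × 1.1 = 82.5, rounded up to 83 per arm, and 2 × 83 = 166. The gap between 64 and 75 is a separate matter. I use 75 per arm below, as the number the plan wants analysed.

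**Variance of the effect estimate, relative to the 12-week t-test.**

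- 12-week t-test: 1
- Change-score t-test: 2(1 − rho)
- ANCOVA (large sample): 1 − rho²

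The effective standardised effect is 0.5 divided by the square root of that factor. Power by noncentral t at 75 per arm:

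| rho | Variance: 12-week / change / ANCOVA | Power: 12-week / change / ANCOVA |
|---|---|---|
| 0.3 | 1 / 1.40 / 0.91 | 86% / 73% / 89% |
| 0.5 | 1 / 1.00 / 0.75 | 86% / 86% / 94% |
| 0.7 | 1 / 0.60 / 0.51 | 86% / 97.5% / 99% |

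The ratio of ANCOVA to change-score variance is (1 − rho²) / [2(1 − rho)] = (1 + rho)/2, that is 0.65, 0.75 and 0.85.

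**Chance imbalance.** The standard error of the baseline difference is sqrt(2/75) = 0.163 SD. An imbalance of that size shifts the 12-week estimate by rho × 0.163 and the change-score estimate by (rho − 1) × 0.163:

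| rho | 12-week estimate | Change-score estimate |
|---|---|---|
| 0.3 | +0.05 SD | −0.11 SD |
| 0.5 | +0.08 SD | −0.08 SD |
| 0.7 | +0.11 SD | −0.05 SD |

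The two readings are therefore pushed in opposite directions by the same imbalance. ANCOVA removes the shift.

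**How often the two readings disagree.** I simulated normal data under the same assumptions, with 75 per arm. With a true effect of 0.5 SD, the two t-tests gave opposite significance verdicts in about 23%, 18% and 14% of trials at rho 0.3, 0.5 and 0.7. With no true effect, each test alone was significant in about 5% of trials, but at least one of the two was significant in about 9%.

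**The case against.** The best defence is that the Methods sentence may only be loose wording for the change comparison in the abstract, and that either t-test, once fixed, is unbiased on average and keeps its 5% error rate. That stands: this is an ambiguity rather than a flat contradiction, and the case for ANCOVA is one of precision. Power is also above the planned 80% in every cell of the table except the change score at rho 0.3. If 0.5 was meant in SDs of change, the change-score test has 86% power at any rho, although ANCOVA is still the more precise by the factor (1 + rho)/2.

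A reader might infer more than the documents support:

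- *That the plan ignores baseline altogether.* This is true only of the 12-week comparison. A change score uses baseline, with a fixed coefficient.
- *That paired data will be analysed as independent.* The Statistical approach section says the difference tested is between the outcome groups, so the independent samples are the arms.
- *That change scores over-correct only when rho is below 0.5.* With equal SDs they over-correct at any rho below 1. The value 0.5 is only where their variance equals that of the 12-week test.
- *That the whole 0.163 SD imbalance reaches the effect.* Only the fractions shown above do.
- *That the gain is very large for strength outcomes, where rho may be high.* At rho 0.9 ANCOVA has variance 0.19 against 1 for the 12-week test, but the change score already has 0.20.
- *That pooling occupations is an error.* The plan states it openly, and further covariates may properly be settled in an analysis plan that is not shown.

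**Conclusion.** The point holds as an unresolved choice between two estimators plus an avoidable loss of precision, and it should be fixed. It is not a failure of validity.

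The mismatch between the two sentences needs no assumption. The size of the precision loss depends on rho, which the documents do not give, and on equal SDs. For rho from 0.3 to 0.7, ANCOVA cuts the variance by 9% to 49% relative to the 12-week t-test and by 35% to 15% relative to the change-score t-test. Under the same assumptions, and with the effect in 12-week SD units, its power exceeds that of the better t-test by between about 1 percentage point (rho 0.7, against change) and 8 points (rho 0.5, against either).

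**What to change.** Replace both sentences with one, worded identically in the abstract and the Methods:

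> For each continuous outcome, the arms are compared at 12 weeks by analysis of covariance with the baseline value of that outcome as covariate, and the adjusted mean difference is reported with its 95% confidence interval. Baseline values are described by arm without significance tests.

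Adding sex and occupational group as covariates is optional. Both are already collected with the demographic information.

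The cost is wording only, with no further measurements, visits or participants. The change should be dated and made before anyone sees outcome data by arm.
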